## Abstract

**Background:**

Atrial fibrillation (AF) is an important health problem in Tunisia. A significant change in the epidemiological pattern of heart disease has been seen in the last 3 decades; however, no large prospective multicenter trial reflecting national data has been published so far. Robust data on the contemporary epidemiological profile and management of AF patients in Tunisia are limited.

**Objective:**

The aim of this study is to analyze, follow, and evaluate patients with AF in a large multicenter nationwide trial.

**Methods:**

A total of 1800 consecutive patients with AF by electrocardiogram, reflecting all populations of all geographical regions of Tunisia, will be included in the study, with the objective of describing the epidemiological pattern of AF. Patients will be officially enrolled in the National Tunisian Registry of Atrial Fibrillation (NATURE-AF) only if an electrocardiogram diagnosis (12-lead, 24-hour Holter, or other electrocardiographic documentation) confirming AF is made. The qualifying episode of AF should have occurred within the last year, and patients do not need to be in AF at the time of enrollment. Patients will be followed for 1 year. Incidence of stroke or transient ischemic attack, thromboembolic events, and cardiovascular death will be recorded as the primary end point, and hemorrhagic accidents, measurement of international normalized ratio, and time in therapeutic range will be recorded as secondary end points.

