**Results:**

Results will be available at the end of the study; the demographic profile and general risk profile of Tunisian AF patients, frequency of anticoagulation, frequency of effective treatment, and risks of thromboembolism and bleeding will be evaluated according to the current guidelines. Major adverse events will be determined. NATURE-AF will be the largest registry for North African AF patients.

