## Methods

### Study Design and Patient Enrollment

NATURE-AF is a prospective, observational registry with a 1-year follow-up period. The enrollment occured all over Tunisia between March 1, 2017, and May 31, 2017. The registry population comprised consecutive in- and outpatients with AF presenting to cardiologists. Consecutive patients were screened for eligibility at the time of their presentation to a cardiologist (hospital or medical center). All patients provided written informed consent. Patients were officially enrolled in NATURE-AF only if they were aged 20 years and older and had had at least 1episode of AF recorded on a standard 12-lead electrocardiogram or on 24-hour Holter monitor. The qualifying episode of AF should have occurred within the last year and could be valvular or nonvalvular AF. Valvular AF is AF in patients with mitral stenosis or prosthetic heart valves. Patients did not need to be in AF at the time of enrollment. All patients admitted for catheter ablation, initiation of drug therapy, or cardioversion (electrical or pharmacological) were eligible to be included.

Exclusion criteria were AF due to reversible causes (eg, thyroid disease and pulmonary embolism) including postoperative AF (≤3 months), life expectancy less than 12 months, acute coronary syndrome, isolated atrial flutter, mental disorders, and ongoing anticoagulation for reasons other than AF.

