### Sample Size and Data Collection

A minimum of 10 consecutive patients per cardiologist were enrolled with a target of 1800 patients for NATURE-AF. A total of 186 cardiologists agreed to participate.

While it was anticipated that most investigators would be hospital-based cardiologists, recruitment by office-based cardiologists was allowed if follow-up of patients was deemed feasible.

The plan was to have 1 baseline visit and 1 visit every 3 months over a 1-year period. Enrollment into the registry started March 1, 2017, with an inclusion period estimated up to 3 months. All patients were followed for 12 months. During this period, all participants revisited their cardiologists at the usual intervals (3 months), and patients taking oral anticoagulant therapy consult (or visited) at least once every month for INR to be measured.

The data collected were managed by the Clinical Suite platform (Dacima Software), which complies with international standards including US Food and Drug Administration 21 Code of Federal Regulations Part 11, US Health Insurance Portability and Accountability Act, International Conference on Harmonisation, and Medical Dictionary for Regulatory Activities. The Clinical Suite platform allowed us to track the data entered, check for inconsistencies and missing data, and schedule monitoring visits. A steering committee was set up to monitor patient inclusions, verify data sources, perform the audit trail, and prepare the statistical analysis plan for the study. Data were collected every 3 months regardless of patient clinic follow-up. All incident events and therapeutic changes were entered at each collection interval.

Baseline data included patient demographics, medical history, cardiovascular history, details of AF history and therapies, vital signs, laboratory measurements, electrocardiographic data, cardiac imaging parameters, details of medical management, and any contraindications to anticoagulation. At follow-up, major incident events and procedures, subsequent vital signs, laboratory studies, imaging parameters, and medication changes were recorded, and the daily acenocoumarol (Sintrom) dose and INR value were noted for all patients taking acenocoumarol. In-depth data regarding antithrombotic therapies, dosing, discontinuations, and reasons for discontinuations were included in follow-up medication data.

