## Results

About 95 cardiologists included 918 patients in the registry with a 1-year follow-up period. All patients provided written informed consent. Patients were officially enrolled in NATURE-AF only if they were aged 20 years and older and had had at least 1 episode of AF recorded on a standard 12-lead electrocardiogram or on 24-hour Holter monitor.

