## Discussion

### Summary

Numerous registries and surveys have been described in different European, Asian, and American countries [7-13,16-19], but few contemporary data on the demographic characteristics, outcome of AF patients, and quality of anticoagulation control achieved in AF patients receiving routine medical care are available in North Africa and especially in Tunisia.

Only 2 published studies have described the epidemiological data on Tunisia [5,15,16]. In 2003, Drissaet al [6] described a multicentric study with 1134 patients presenting with a first episode of AF between January 1985 and December 2000. The average age was 58.6 (SD 15-60) years; 57.8% (656/1134) were male and 42.2% (478/1134) were female. The most common etiology of AF identified was rheumatic carditis (36.1%). AF was idiopathic in 27.7% of cases. Higher morbidity and mortality were demonstrated in AF patients with a 5-year survival of 85%.

Recently, geographic differences have been highlighted by Gamra et al [16,17]. The RealiseAF international cross-sectional survey enrolled 10,523 patients (with at least 1 documented AF episode in the preceding 12 months) from 831 sites; 26 countries from 4 continents participated in the study with Middle East and North Africa participation from Algeria (n=310), Egypt (n=458), Lebanon (n=191), Morocco (n=250), and Tunisia (n=471). AF patients from the Middle East and Africa were significantly younger and more frequently female compared with those originating from the rest of the world. A CHADS_2_ (congestive heart failure, hypertension, age >75 years, diabetes mellitus, stroke) score ≥2 was observed in 64.2% of the patients originating from Europe versus 58.3%, 57.8%, and 43.6% from Latin America, Asia, and the Middle East and Africa, respectively. Among those patients with a CHADS_2_ score ≥2, there were also important geographical differences with respect to the use of antithrombotics: the proportion of patients not receiving any antithrombotic therapy ranged from 11.4% in the Middle East and Africa to 27.6% in Latin America. Conversely, the use of oral anticoagulants was highest in the Middle East and Africa (66.7%) and lowest in Asia (31.7%) [16,17].

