### Conclusions

NATURE-AF will fill a significant gap in the dynamic landscape of AF care and research. It will provide unique and necessary data on the management and outcomes of AF patients treated. This study will yield the largest contemporary longitudinal cohort of patients with AF in Tunisia and would provide a valuable opportunity for real-world clinical epidemiology with insights into the uptake and outcomes of contemporary AF management.

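### The abstract still announces 1800 patients, but enrolment had closed with 918 from about 95 of 186 cardiologists, and the stated minimum of 10 per cardiologist does not fit those counts

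*Protocol article*

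**What the plan says.** **Size.** The Methods paragraph of the abstract, in the future tense: "A total of 1800 consecutive patients with AF by electrocardiogram, reflecting all populations of all geographical regions of Tunisia, will be included in the study".

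**Target and sites.** Sample Size and Data Collection, in the past tense: "A minimum of 10 consecutive patients per cardiologist were enrolled with a target of 1800 patients for NATURE-AF". It adds: "A total of 186 cardiologists agreed to participate".

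**Enrolment window.** Study Design and Patient Enrollment: "The enrollment occured all over Tunisia between March 1, 2017, and May 31, 2017". The Timeline section gives the same closing month.

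**Achieved enrolment.** Results section of the main text: "About 95 cardiologists included 918 patients in the registry with a 1-year follow-up period".

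**Claims that lean on size.** The Results paragraph of the abstract: "NATURE-AF will be the largest registry for North African AF patients". The Conclusions section at the end of the article makes a narrower claim: "This study will yield the largest contemporary longitudinal cohort of patients with AF in Tunisia".

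**Comparators.** The Summary section of the Discussion describes an earlier Tunisian series as "a multicentric study with 1134 patients presenting with a first episode of AF". It also gives country counts from an international cross-sectional survey: Algeria 310, Egypt 458, Lebanon 191, Morocco 250 and Tunisia 471.

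**The concern.** Two sizes stand in one article. The abstract presents 1800 as what the study will contain, while the body shows that recruitment had finished at about half of that. Someone who reads only the abstract takes away a sample almost twice the real one.

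The primary end point is descriptive: the incidence of stroke or transient ischaemic attack, thromboembolism and cardiovascular death over one year. For such an aim, the number of patients is what sets the precision of the headline result, so the wrong number misstates how much the registry can say.

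The minimum of 10 per cardiologist is a second, separate inconsistency. It is reported as something that happened, and it describes how patients were gathered at each site. If some cardiologists enrolled fewer than 10, the account of recruitment is inaccurate.

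The coverage and largest-registry statements appear in the abstract beside the planned size, and neither was revisited when enrolment came in at 918.

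**Working it through.** **Inputs from the article.** Stated size 1800; target 1800 with at least 10 per cardiologist; 186 cardiologists agreed; enrolment closed May 31, 2017; 918 patients from about 95 cardiologists. No event rate, precision, power or dropout figure is given as the basis for 1800.

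**1. Can 1800 be reproduced?** Not from any stated derivation. The nearest product is 186 × 10 = 1860, which is 60 more than 1800 (60/1800 = 3.3%). The article does not say that the target was obtained this way, so 1800 is taken simply as the stated target.

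**2. Achieved against stated.**
- Patients: 918/1800 = 0.510, a shortfall of 1800 − 918 = 882.
- Cardiologists: 95/186 = 0.511, leaving about 186 − 95 = 91 who agreed but are not among those reported as including patients.

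**3. The minimum of 10.**
- Mean per contributing cardiologist: 918/95 = 9.66.
- Patients needed if each of 95 had at least 10: 95 × 10 = 950, which is 32 more than 918.
- Largest number of cardiologists for which a minimum of 10 is possible: 918/10 = 91.8, so 91.
- The count is given only as approximate. At 91 the mean is 10.09, at 92 it is 9.98, and at 100 it is 9.18. From 92 upwards, at least one cardiologist must have enrolled fewer than 10.

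**4. Precision.** The 95% half-width is 1.96 × √(p(1 − p)/n). The ratio of widths at 918 and 1800 does not depend on p: √(1800/918) = 1.40. The values of p below are assumptions, because the article states no expected incidence.

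| Assumed one-year proportion | Half-width at 1800 (points) | Half-width at 918 (points) |
|---|---|---|
| 2% | 0.65 | 0.91 |
| 5% | 1.01 | 1.41 |
| 10% | 1.39 | 1.94 |

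At an assumed 5%, expected events are 0.05 × 1800 = 90 against 0.05 × 918 = 45.9.

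**5. Size against the article's own comparators.** The earlier Tunisian series has 1134 patients. The four North African countries in the survey give 310 + 458 + 250 + 471 = 1489. A study of 1800 would have exceeded both; 918 exceeds neither.

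**The case against.** The strongest defence is that nothing was concealed. The body of the article calls 1800 a target and openly reports 918. Missing a recruitment target is an outcome, not a design error, and no planned analysis depends on having 1800 patients. No precision was promised, so none was breached, and wider intervals do not bias a descriptive incidence. All of this stands, and it limits the point to what is stated wrongly. It does not rescue the abstract, which says without qualification that 1800 will be included after enrolment had closed at 918.

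On the minimum of 10, the defence is that the number of cardiologists is rounded. That also stands in part: with 91 or fewer there is no contradiction. At the reported figure, and at any count from 92 upwards, there is.

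Three stronger readings are tempting, and the document does not support them:

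- **That the largest-registry claim is false.** The series of 1134 is a first-episode study covering 1985 to 2000, and the 1489 is a sum over countries in a cross-sectional survey. The article calls neither a registry. The narrower claim in the Conclusions, about a contemporary longitudinal cohort in Tunisia, is contradicted by no figure in the article.
- **That the sample is not national.** The article says enrolment took place throughout the country and gives no regional counts. Participation by about half of the cardiologists leaves coverage open; it does not refute it. The absence of quotas or weights from a condensed article is not a fault either.
- **That 1800 is itself a mistake.** As a planned target it is legitimate and should remain on record.

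**Conclusion.** The point holds in limited form. The abstract's 1800 is contradicted by the closed enrolment of 918, which is 51.0% of the target, from about 51.1% of the cardiologists who agreed, and no part of the article reconciles the two. The sentence on a minimum of 10 per cardiologist is inconsistent with a mean of 9.66, unless the approximate count of 95 stands for 91 or fewer.

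The consequence is a loss of precision by a factor of about 1.40, not bias and not an invalid analysis. That factor takes 918 as the final number enrolled and uses a simple binomial interval; the half-widths in percentage points rest on assumed proportions of 2% to 10%.

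The statements on coverage of all regions and on being the largest North African registry are unsupported at 918. A reader might infer that they have been disproved, but the document lacks the regional counts and like-for-like comparators that would show this.

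**What to change.** - In the abstract and in Sample Size and Data Collection, state 918 patients enrolled against a target of 1800, from about 95 of the 186 cardiologists who agreed. Keep the target visible beside the achieved number, and give the exact count of cardiologists if it is known.
- Reword the per-cardiologist sentence as an intended minimum, or replace it with the observed distribution of patients per cardiologist.
- State the precision expected at 918, with the assumed incidences labelled as assumptions. The table above can serve.
- Qualify the statement that the patients reflect every population and region. A count of patients by region would let readers judge it.
- Qualify or remove the largest-registry claim in the abstract. The narrower wording in the Conclusions can stand on the article's figures.

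No additional analysis is required. Excluding cardiologists with fewer than 10 patients would select sites on a count known only afterwards, without a stated reason to expect bias. Standardising to regional population shares would need figures that the article does not give.

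The cost is a few sentences of wording and a small table, with no new patients. The downside is a less favourable stated size.

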**Results:**

Results will be available at the end of the study; the demographic profile and general risk profile of Tunisian AF patients, frequency of anticoagulation, frequency of effective treatment, and risks of thromboembolism and bleeding will be evaluated according to the current guidelines. Major adverse events will be determined. NATURE-AF will be the largest registry for North African AF patients.

**Conclusions:**

This study would add data and provide a valuable opportunity for real-world clinical epidemiology in North African AF patients with insights into the uptake of contemporary AF management in this developing region.

**Trial Registration:**

ClinicalTrials.gov NCT03085576; https://clinicaltrials.gov/ct2/show/NCT03085576 (Archived by WebCite at http://www.webcitation.org/6zN2DN2QX)

**Registered Report Identifier:**

RR1-10.2196/8523

## Introduction

### Background

Atrial fibrillation (AF) is the most common sustained cardiac rhythm disorder, and recent projections in Europe estimate that from 2010 to 2060, the number of adults aged 55 years and older with AF in the European Union will more than double [1]. With the aging population and associated prevalence of other cardiovascular diseases, the burden of AF is projected to increase. It is estimated that by 2050, the prevalence of AF in Africa will be greater than in any other region of the world [2]. Given the increasing prevalence and AF’s association with significant morbidities and mortality, this increase would have major public health implications.

In the last decades, a significant change in the epidemiologic and etiologic patterns of cardiovascular diseases has been seen in North Africa with a decrease in rheumatic heart disease and increase in hypertensive and ischemic heart disease [2,3]. The World Health Organization reported trends in the incidence and prevalence of acute rheumatic fever and rheumatic heart disease for each continent based on literature from 100 countries around the world between 1970 and 2009 [4,5]. However, data from Africa are scarce and do not capture the entire time frame. As for all heart diseases, there are insufficient contemporary population-based data describing the epidemiologic pattern of AF in North Africa and especially in Tunisia. In 2003, valvular AF secondary to rheumatic heart disease was the most common etiologic form of AF [6].

Numerous registries and surveys have been described in different European, Asian, and American countries—Euro Observational Research Programme–Atrial Fibrillation pilot general registry [7], Japanese Rhythm Registry [8], Global Anticoagulant Registry in the Field [9], Global Registry on Long-Term Oral Antithrombotic Treatment in Patients with Atrial Fibrillation [10], the nationwide US Practice Innovation and Clinical Excellence Registry [11], Outcomes Registry for Better Informed Treatment of Atrial Fibrillation [12], and Chinese Atrial Fibrillation Registry study [13]. However, few data on the demographic characteristics, outcome of AF patients, and quality of anticoagulation control achieved in AF patients receiving routine medical care are available in North Africa and especially in Tunisia.

Demographic and prognostic AF data from other ethnic groups would not be generalizable to our population. Thus, a register or a survey dealing with the demographic and prognostic characteristics of AF in Tunisia is essential, making it possible to identify its specific characteristics inherent in part to ethnic particularities but especially to particularities of the local health system.

### Registry Objectives

The National Tunisian Registry of Atrial Fibrillation (NATURE-AF) is a prospective observational accumulation of data used in the investigation of the optimal intensity of anticoagulation in Tunisian AF patients and present status of anticoagulation treatment in Tunisia.

The primary end point of NATURE-AF is to describe the incidence of stroke or transient ischemic attack (TIA), thromboembolic event, and cardiovascular death every 3 months up to 1 year.

The secondary end points are as follows:

Hemorrhagic accidents, every 3 months up to 1 yearInternational normalized ratio (INR) every month for 1 yearMean time in therapeutic range (TTR) obtained in patients who receive anticoagulant therapy

## Methods

### Study Design and Patient Enrollment

NATURE-AF is a prospective, observational registry with a 1-year follow-up period. The enrollment occured all over Tunisia between March 1, 2017, and May 31, 2017. The registry population comprised consecutive in- and outpatients with AF presenting to cardiologists. Consecutive patients were screened for eligibility at the time of their presentation to a cardiologist (hospital or medical center). All patients provided written informed consent. Patients were officially enrolled in NATURE-AF only if they were aged 20 years and older and had had at least 1episode of AF recorded on a standard 12-lead electrocardiogram or on 24-hour Holter monitor. The qualifying episode of AF should have occurred within the last year and could be valvular or nonvalvular AF. Valvular AF is AF in patients with mitral stenosis or prosthetic heart valves. Patients did not need to be in AF at the time of enrollment. All patients admitted for catheter ablation, initiation of drug therapy, or cardioversion (electrical or pharmacological) were eligible to be included.

Exclusion criteria were AF due to reversible causes (eg, thyroid disease and pulmonary embolism) including postoperative AF (≤3 months), life expectancy less than 12 months, acute coronary syndrome, isolated atrial flutter, mental disorders, and ongoing anticoagulation for reasons other than AF.

### Sample Size and Data Collection

A minimum of 10 consecutive patients per cardiologist were enrolled with a target of 1800 patients for NATURE-AF. A total of 186 cardiologists agreed to participate.

While it was anticipated that most investigators would be hospital-based cardiologists, recruitment by office-based cardiologists was allowed if follow-up of patients was deemed feasible.

The plan was to have 1 baseline visit and 1 visit every 3 months over a 1-year period. Enrollment into the registry started March 1, 2017, with an inclusion period estimated up to 3 months. All patients were followed for 12 months. During this period, all participants revisited their cardiologists at the usual intervals (3 months), and patients taking oral anticoagulant therapy consult (or visited) at least once every month for INR to be measured.

The data collected were managed by the Clinical Suite platform (Dacima Software), which complies with international standards including US Food and Drug Administration 21 Code of Federal Regulations Part 11, US Health Insurance Portability and Accountability Act, International Conference on Harmonisation, and Medical Dictionary for Regulatory Activities. The Clinical Suite platform allowed us to track the data entered, check for inconsistencies and missing data, and schedule monitoring visits. A steering committee was set up to monitor patient inclusions, verify data sources, perform the audit trail, and prepare the statistical analysis plan for the study. Data were collected every 3 months regardless of patient clinic follow-up. All incident events and therapeutic changes were entered at each collection interval.

Baseline data included patient demographics, medical history, cardiovascular history, details of AF history and therapies, vital signs, laboratory measurements, electrocardiographic data, cardiac imaging parameters, details of medical management, and any contraindications to anticoagulation. At follow-up, major incident events and procedures, subsequent vital signs, laboratory studies, imaging parameters, and medication changes were recorded, and the daily acenocoumarol (Sintrom) dose and INR value were noted for all patients taking acenocoumarol. In-depth data regarding antithrombotic therapies, dosing, discontinuations, and reasons for discontinuations were included in follow-up medication data.

